| **A Surveillance Study for Early Detection of Cancer in Primary Sclerosing Cholangitis**  ***2011-02-15*** | | |
| --- | --- | --- |
|  | Coordinating Investigator | [name], Gastrocentrum, Karolinska University Hospital |

Table of Contents

Summary 3

1 ABBREVIATIONS 4

2 AdministrativE information 5

3 BACKGROUND INFORMATION 5

Study Objectives 6

The objective of the current study is: 6

4 QUESTION 6

4.1 Primary question 6

5 Endpoints 6

6 Design 6

6.1 General design 6

6.2 Assessments and procedures 7

6.3 Flow chart 8

7 STUDY SUBJECTS 8

7.1 Inclusion criteria 8

7.2 Exclusion criteria 9

7.3 Criteria for withdrawal 9

8 StATISTICS AND DATA MANAGEMENT 9

8.1 Data management 9

9 EtHICS 9

9.1 The Swedish Ethical Review Authority 9

9.2 Ethical implementation of the study 9

9.3 Evaluation of risks and benefits 10

9.4 Study subjects’ information and informed consent 10

9.5 Case Report Forms 10

9.6 Archiving 10

10 PublicATION OF RESULTS 10

11 PROTOCOL AMENDMENTS 10

12 STAFF information 10

13 RefeRENCES 11

14 FlOWCHART 12

Summary

| **PROTOCOL TITLE AND OBJECTIVES** | |
| --- | --- |
| Protocol title: | A surveillance study for early detection of cancer in primary sclerosing cholangitis (PSC) |
| Study objectives: | To investigate whether surveillance with an annual magnetic resonance cholangiopancreatography imaging (MRI/MRCP) and modern endoscopic and radiological techniques can identify early cancer development in PSC and offer a cure for the cancer. |
|  |  |
|  |  |
| **STUDY SUBJECT POPULATION** |  |
| Study subjects: | Patients with PSC |
| Number: | 600 |
|  |  |
| **STUDY TIMELINE** |  |
| First patient included: | 30-05-2011 |
| Last patient included: | 30-04-2014 |
| Last patient completed: | 31-12-2019 |

ABBREVIATIONS

| **Abbreviation** | **Explanation** |
| --- | --- |
| CRF | Case Report Form |
| PSC | Primary Sclerosing Cholangitis |
| CC | Cholangiocarcinoma |
| CA19-9 | Carbohydrate Antigen 19-9 |
| CEA | Carcinoembryonic Antigen |
| FISH | Fluorescent in situ hybridization |
| IBD | Inflammatory Bowel Disease |
| PET | Positron Emission Tomography |
| FDG-PET | 2[^18^F] fluoro-2-deoxy-D-glucose Positron Emission Tomography |
| MRI | Magnetic Resonance Imaging |
| ERCP | Endoscopic Retrograde Cholangiopancreatography |
| MRCP | Magnetic Resonance Cholangiopancreatography |
| VAS | Visual analogue scale |

AdministrativE information

There is a lack of medical treatment that slows the course of the disease and reduces the risk of cancer and the only curative treatment if liver cirrhosis with complications has presented itself is a liver transplant. PSC is the most common single cause of liver transplantation in Scandinavia (3). After a liver transplant, the risk for colorectal cancer remains and there are a few individual reports that say it may even be increased (4). If CC has occurred, then often the patient cannot have a transplant due to a rapid recurrence and growth of cancer in the transplanted organ during ongoing immunosuppression. There are a few individual studies that suggest that transplantation early in the progress of CC, alone or in combination with external radiation, brachytherapy and cytostatics in accordance with an extremely strict protocol (so-called Mayo Protocol), can lead to a cure in some patients (5,6). Without treatment, survival after a CC diagnosis is 3-6 months.

Surveillance for CC with PSC (with analysis of CA 19-9 in combination with ultrasound, CT, MRI and/or ERC with brush cytology and FISH/DNA abberations) is controversial but in one study, has been reported to be able to diagnose CC early on and improve survival (7).

We have previously evaluated the diagnostic value of dynamic positron emission tomography (PET) with 2[^18^F]fluoro-2-deoxy-D-glucose (FDG) for CC in 24 PSC patients that were planned for liver transplantation (8). All patients had a preoperative transplantation analysis without a definite finding of malignancy and underwent a preoperative FDG-PET. PET diagnosis was compared with histopathology from explanted liver and FDG-PET had a positive predictive value with CC or CC in situ (= high grade dysplasia) at 75% and a negative predictive value of 95%.

Assuming the diagnostic sensitivity and specificity and the positive and negative predictive values of the previously reported investigation modalities for CC in an unselected material of PSC patients (9) it seems more cost-effective as an initial surveillance investigation to use MRI/MRC and S-CA 19-9. In case of suspected malignant findings, patients are investigated using ERC and/or PET-CT according to clinical practice. Modern investigations of bile ducts include cholangioscopy with the SpyGlass technique, which also enables biopsy from the bile ducts.

**Hypothesis**

Through annual surveillance with Magnetic Resonance Cholangiopancreatography (MRCP)/MRI + CA 19-9, we can identify early stage cholangiocarcinoma, thereby offering a potentially curative treatment.

Study Objectives

The objective of the current study is:

1. If surveillance with MRCP can identify early malignant changes in PSC.
2. Investigate the value of PET diagnostics in early malignant changes in bile ducts in patients with dominant strictures in PSC.
3. To evaluate yearly colonoscopic surveillance in PSC-IBD
4. To collect a prospective cohort with complete clinical data and biobanked samples for further research

QUESTION

Primary question

Using annual MRCP investigations and modern endoscopic and radiological techniques to identify early cancer development with PSC, is it possible to offer a cure against cancer? Can PET diagnostics of malignant changes in bile ducts in patients with dominant strictures in PSC contribute to diagnostic accuracy?

Endpoints

## Primary endpoints: Hepatobiliary cancer (CC, hepatocellular carcinoma, gall bladder carcinoma)

**Secondary endpoints:** Liver transplantation, death, colorectal cancer

Design

General design

Patients are followed annually by using clinical characteristics, symptom scores, other treatments, liver tests including CA 19-9, MRI, MRCP and coloscopy with biopsies. Patients are included either in connection with a colonoscopy or an MRI/MRCP (<2 months old). It is important that the surveillance investigations (coloscopy and MRI/MRCP) are performed regularly with a 1-year interval (± 2 months) but it is NOT important that a colonoscopy and MRI/MRCP are synchronised with each other. Upon inclusion, the date is indicated for the MRCP and colonoscopy, respectively and investigations are repeated annually according to these dates. MRCP surveillance is only performed in patients that have not undergone a liver transplant. Colonoscopy surveillance is only performed in patients with IBD. In the event a dominant stricture is identified, an ERCP is carried out using brush cytology and if this shows dysplasia, a PET-CT is performed if there is availability at the hospital and in line with local practice. Patients are recruited at gastroenterology clinics throughout Sweden and a total of 600 patients will be included. Follow-up and interventions (except for an annual MRI/MRCP), does not normally differ from the regular clinical follow-ups that are carried out at the clinic. Patients that are included in the study are recruited via their physician and study follow-up can be taken care of without interrupting the patient-doctor continuity.

Assessments and procedures

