

FlOWCHART

|  | **Inclusion** | **12 months** | **24 months** | **36 months** | **48 months** | **60 months** (or at the end of the study if endpoint is reached) |
| --- | --- | --- | --- | --- | --- | --- |
| Informed consent | X |  |  |  |  |  |
| Inclusion/exclusion criteria | X |  |  |  |  |  |
| Randomisation | X |  |  |  |  |  |
| Liver function tests, CA 19-9, CEA | X | X | X | X | X | X |
| IgG4  Autoantibodies  IgG, IgA  HBsAg, Anti-HCV | X |  |  |  |  |  |
| Colonoscopy | X | X | X | X | X | X |
| MRI/MRCP | X | X | X | X | X | X |
| List of medications | X | X | X | X | X | X |
| Clinical information according to CRF | X | X | X | X | X | X |
| Serum and plasma for freezing | X | X | X | X | X | X |
| Whole blood for freezing | X |  |  |  |  |  |

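### The endpoints record whether hepatobiliary cancer occurs, not whether it was found early or treated with curative intent, which is what the primary question asks

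*Protocol*

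**What the plan says.** The hypothesis, at the end of the Background, is that with annual MRI/MRCP and CA 19-9 "we can identify early stage cholangiocarcinoma, thereby offering a potentially curative treatment". Section 4.1 (Primary question) asks of annual MRCP and modern endoscopic and radiological techniques: "is it possible to offer a cure against cancer". The Summary states the objective in the same sense.

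Section 5 (Endpoints) reads "Primary endpoints: Hepatobiliary cancer (CC, hepatocellular carcinoma, gall bladder carcinoma", closing the bracket there. The secondary endpoints are "Liver transplantation, death, colorectal cancer".

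Section 6.1 describes one cohort of 600 patients, with annual MRI/MRCP for all who have not had a liver transplant. Section 6.2 records cancer development and imaging, ERCP and intervention results each year for five years. At 7 and 10 years after inclusion it collects cancer, colectomy, transplantation and death. The flow chart in Section 6.3 includes tumour staging and therapy planning.

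**The concern.** An endpoint should move when the answer to the question changes. Occurrence of cancer need not. A cohort in which most cancers are found at a treatable stage and one in which most are found late can report the same count. The direction is also ambiguous, because more cancers may mean better detection or higher risk.

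The secondary endpoints do not fill the gap. Death is not tied to hepatobiliary cancer. Transplantation mixes two meanings: the Background gives it for cirrhosis with complications, while the flow chart lists it among tumour therapies.

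At stake is the credibility of the main conclusion. The protocol nowhere defines early stage. If the definition is chosen once the cancers are known, the share called early can be steered by that choice.

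**Working it through.** **Reproducing the plan's figure.** The protocol states 600 patients without a rate, precision target, alpha or power, so there is nothing to reproduce. The check is a comparison of the text, followed by an illustration.

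**Side by side.**

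| Place in protocol | Subject | Stage at detection | Curative-intent treatment |
|---|---|---|---|
| Hypothesis | early-stage cholangiocarcinoma, potential cure | yes | yes |
| Section 4.1 | early cancer, possibility of cure | yes | yes |
| Section 5, primary | occurrence of three hepatobiliary cancers | no | no |
| Section 5, secondary | transplantation, death, colorectal cancer | no | no |
| Sections 6.2 and 6.3 | cancer details, staging, therapy planning | recorded in care, not an endpoint | planned in care, not an endpoint |

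**Same primary result, opposite answers.** Assumption: annual cancer rate r = 1%, full five-year follow-up (the protocol gives no rate).

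- Expected cancers = 600 × (1 − e^(−5r)) = 600 × (1 − e^(−0.05)) = 29.3, about 29.
- Primary endpoint: 29/600 = 4.8%, exact 95% CI 3.3-6.9%.
- If 6 are early: 6/29 = 21%, CI 8-40%. If 23 are early: 23/29 = 79%, CI 60-92%.

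The 4.8% is the same in both cases.

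**Precision of an endpoint that fits the question.** Assumed rates 0.5-1.5% per year.

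- Person-years: 600 × 5 = 3,000.
- Cancers: 3,000 × 0.005 = 15; 3,000 × 0.015 = 45.
- Both are upper bounds. Allowing for patients who leave the risk set at diagnosis, the formula above gives 14.8 and 43.4. Dropout lowers this further, as does removing transplanted patients, who under Section 7.1 may be included with colonoscopy surveillance only.
- Clopper-Pearson 95% CI with about half early: 7/15 gives 21.3-73.4%; 22/45 gives 33.7-64.2%.

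These intervals are for cancers only and do not include dysplasia.

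**Timeline.** The Summary gives first inclusion on 30-05-2011, last inclusion on 30-04-2014 and last patient completed on 31-12-2019.

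- Five-year visits end around 30-04-2014 + 5 years = 30-04-2019, which fits.
- The earliest 10-year contact is 30-05-2011 + 10 years = 30-05-2021, after the stated completion for every patient.
- The 7-year contacts run from 30-05-2018 to 30-04-2021, so they also fall after completion for anyone included after 31-12-2012.

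The completion date may refer to the five-year phase only, but the protocol does not say so.

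**The case against.** The strongest reply is that Section 5 names an event and does not say that it will be summarised as an incidence. The statistical analysis plan is not shown, and the study records cancer details, imaging, ERCP results, staging and therapy planning. The cancers could therefore be described by stage and treatment. This stands in part: the data for a descriptive answer largely exist, so the study is not incapable of addressing its question. It does not remove the mismatch, because the endpoints are fixed in the protocol itself and neither stage nor curative treatment is among them.

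Three stronger readings are tempting but not supported.

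- **Lack of randomisation as the defect.** The question is whether cure is possible, and one surveilled cohort can answer that descriptively. The schedule in Section 14 does carry "Randomisation | X" at inclusion, but no arms or ratio appear anywhere. That is a separate inconsistency to reconcile.
- **A survival comparison distorted by lead time.** The Background quotes 3-6 months' survival without treatment, but no section plans a comparison with it.
- **High-grade dysplasia as a lost event.** The words "CC or CC in situ (= high grade dysplasia" describe histology in an earlier PET study. If that equation carries over, dysplasia could count as cholangiocarcinoma. Its status is undefined; the text does not exclude it.

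**Conclusion.** The point holds as a mismatch between question and endpoint. The hypothesis and primary question ask about early detection and cure; no primary or secondary endpoint measures either, and early stage is undefined. For a given number of cancers, the primary result is the same whether few or most were found early. This rests on the protocol's wording alone; the 1% and 0.5-1.5% annual rates are assumptions that only give scale.

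A reader might infer that the study can neither confirm nor refute its hypothesis. That goes too far, since stage and treatment could still be described from what is recorded. What is missing is their specification as outcomes before the results are known.

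**What to change.** In Section 5:

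- Make primary the proportion of hepatobiliary cancers arising in MRCP-surveilled, non-transplanted patients that were at a pre-defined early stage at detection and received curative-intent treatment, with an exact 95% CI. Keep cancer occurrence as a further endpoint.
- State whether biliary high-grade dysplasia counts as cholangiocarcinoma in situ, and report it separately from invasive cancer, because including it can inflate the early share through overdiagnosis.
- Define cure as alive without recurrence at a fixed time after curative-intent treatment. The 7- and 10-year contacts run from inclusion, so a cancer treated shortly before one of them would otherwise count as cured within weeks.
- Report transplantation by indication (neoplasia or liver failure) and hepatobiliary-cancer mortality from inclusion.

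Elsewhere: add recurrence to the 7- and 10-year items in Section 6.2, reconcile those contacts with the 31-12-2019 completion date, reconcile the Randomisation row with the single-cohort design, and word the conclusions as descriptive.

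The cost is amendment wording and a few CRF fields (stage, treatment intent and date, transplant indication), largely available from the staging and therapy steps. Recurrence is a new item to collect, and cancers treated late may not reach the fixed time for cure within 10 years. The main drawback is that the headline becomes a proportion of few cancers with a wide interval, as shown above.

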**Inclusion**

- Oral and written patient information
- Informed consent is obtained
- Verification of inclusion and exclusion criteria
- Details of age, gender and medical history is registered
- Clinical information about PSC and IBD is registered, including information about the most recent MRI/MRCP/colonoscopy
- VAS-scale (0-10) for estimation of itching
- Health examination
- Registration of ongoing illnesses/diseases
- Registration of concomitant medications
- Blood tests: Bilirubin, ASAT, ALAT, GT, ALP, Albumin, PK, INR, Creatinine, Na, K, CEA, CA19-9, Hb, TPK, LPK, amylase
- Serum – whole blood and plasma samples to be frozen for future analysis (for example, for tumour markers and bile acids)
- Autoantibodies (ANA, AMA, SMA, LKM1) Total IgG and IgA, IgG4, HBsAg, Anti-HCV

**Annual follow-up for five years** (12 months, 24 months, 36 months, 48 months, 60 months).

- Ongoing illnesses
- Concomitant medications
- Registration of the onset of symptoms, activity of IBD and interventions
- Results from the MRI/MRCP performed since the previous visit (copy attached to CRF) (± 2 months) (this also applies to small duct PSC)
- Results from any ERCP (ERCP is carried out only in the event of a follow-up visit, if necessary, i.e., if there are suspicious changes on the MRCP that need to be mapped out further with an ERCP)
- Results from a colonoscopy (± 2 months)
- Blood tests: Bilirubin, ASAT, ALAT, GT, ALP, Albumin, PK, INR, Creatinine, Na, K, CEA, CA19-9, Hb, TPK, LPK, amylase
- Details about cancer development
- Serum and plasma samples to be frozen for future analysis (for example, for tumour markers and bile acids)

In patients who undergo MRI/MRCP during the course of the study due to a clinical indication, an annual follow-up check is carried without MRCP, which is calculated after the most recent investigation.

**ERCP**

In the event of an indication of ERCP, a brush sample is always taken. Ideally at the same time as a similar test method to the brush cytology, see sampling instructions “Brush cytology with ERCP”

**Blood tests/Bio banking**

All blood tests are taken according to the protocol (see the flow chart) and are analysed at a local clinical chemistry laboratory and entered in the CRF. Extra research samples for future analyses are marked and handled according to special instructions “Labelling of samples” and “Manual for handling samples”. The samples are stored at each respective centre in a -70°C freezer and transported annually to the coordinating investigator together with a code key.

Results from analyses and investigations are registered on specially prepared forms, CRF’s, where the patient is only identified with a code number. Data is registered, saved and later analysed in a database that the sponsor is responsible for. Code lists are stored at each respective investigator but the code key is transferred to the biobank at Karolinska University Hospital for centralising the information. All presentations of the data are carried out de-identified.

EtHICS

The Swedish Ethical Review Authority

The coordinating investigator is responsible for approval from the Swedish Ethical Review Authority. Approved by the regional Ethics Committee in Stockholm (Dnr 2011/824-31/2).

Ethical implementation of the study

The study will be carried out according to the study protocol, Good Clinical Practice (GCP), regulatory requirements and the Declaration of Helsinki.

Evaluation of risks and benefits

Patients with PSC have a high risk of developing cancer, both in the bile ducts and large intestine with concomitant IBD, but also in the pancreas. This occurs most commonly between 30-50 years of age as most people affected by PSC are young. The risk of colorectal cancer is increased by 10 times and in the liver 160 times, compared to the normal population (2). Due to the high risk of cancer, an annual colonoscopy check is recommended in these patients and if dysplasia develops, then patients are operated with a colectomy. Liver tumours are often detected late and there is often no treatment. The mean survival rate in the event of a liver cancer diagnosis is less than 6 months. Early diagnostics allow for several treatment possibilities that can lead to a cure or an extended life. The risks/discomfort that exist through study participation are minor. The potential benefit of the study results is deemed to far exceed the disadvantages associated with the study.

Study subjects’ information and informed consent

The investigator is responsible for providing oral and written information and receiving and signing consent forms with the patient. The originals must remain at the clinic and a copy is provided to the patient.

Case Report Forms

Data that is collected in the study will be registered in the Case Report Form (CRF), where the patient is only identified with a code number. The code key is stored with the investigator and is collected by the coordinating investigator throughout the entire study.

Archiving



FlOWCHART

|  | **Inclusion** | **12 months** | **24 months** | **36 months** | **48 months** | **60 months** (or at the end of the study if endpoint is reached) |
| --- | --- | --- | --- | --- | --- | --- |
| Informed consent | X |  |  |  |  |  |
| Inclusion/exclusion criteria | X |  |  |  |  |  |
| Randomisation | X |  |  |  |  |  |
| Liver function tests, CA 19-9, CEA | X | X | X | X | X | X |
| IgG4  Autoantibodies  IgG, IgA  HBsAg, Anti-HCV | X |  |  |  |  |  |
| Colonoscopy | X | X | X | X | X | X |
| MRI/MRCP | X | X | X | X | X | X |
| List of medications | X | X | X | X | X | X |
| Clinical information according to CRF | X | X | X | X | X | X |
| Serum and plasma for freezing | X | X | X | X | X | X |
| Whole blood for freezing | X |  |  |  |  |  |
